### Procedures and data collection

#### Evaluations and study plan

Participants will be assessed at two points during the study: the baseline assessment at the beginning of the study and the final assessment after the end of the intervention. The baseline assessment will take place after recruitment and before randomisation and allocation of subjects to the corresponding group. This initial assessment includes the recording of the independent variables and the primary outcome variables to be studied; the intervening variables will be recorded and several objective assessment tests will be used. Then, after randomisation, the intervention for each group will be carried out. Then, another assessment will be carried out, considered the final assessment, where participants will be asked to complete the same objective tests as in the initial assessment. The results will be notified by means of an individual and personal report to those persons who expressed the wish at the beginning to receive the information corresponding to the results and evolution. All evaluations will be carried out by research staff, previously trained and instructed in this process. This process can be seen in more detail in Fig 2 which includes a flow chart of the study methodology.

**Fig 2 pone.0300898.g002:**
[figure not shown]
Study methods flow chart.

#### Description of the variables

The primary variable will be everyday cognition, measured by the Test for the Evaluation of Everyday Cognition (PECC) and cognitive performance, measured by the Montreal Cognitive Assessment Test (MoCA). Secondary variables will be functionality (Functional Independence Measure, FIM), emotional state (Yesavage Scale), frailty (Frailty Index) and independence in instrumental activities of daily living (Lawton and Brody Scale). We will also record the following intervening variables in the clinical history of each participant: social support (Questionnaire MOS) and adherence to treatment (Questionnaire ARMS-e), and other socio-demographic data (age, sex, level of education, marital status and main occupation).

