#### Sample size

The sample size has been estimated using Epidat 4.2. A one-sided approach has been assumed with a confidence level of 95% and a statistical power of 80%. It has been decided to take equal sizes in the two groups (i.e. R = n2/n1) and the Yates correction will not be applied. The sample size calculation was based on the results of a similar RCT, specifically the study conducted by Fernández et al. in 2018 [16] which compared the outcomes of a traditional cognitive stimulation intervention versus an intervention based on everyday cognition. The primary variable chosen in both studies was everyday cognition. The study found that the experimental group (those who received everyday cognition training) demonstrated an improvement of 2.57 points in the primary variable, while the control group (those who received traditional cognitive stimulation) only demonstrated an improvement of 0.39 points. With an expected population loss of 20%, the final sample size was n = 99 participants, with 50 in the experimental group and 49 in the control group.

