### Data analysis

To test the normal distribution of data, a histogram will be used. Variables that have a normal distribution shall be defined by the mean and standard deviation, while variables that do not follow a normal distribution shall be defined by the median and the interquartile range. The effects of the intervention on primary outcomes (everyday cognition and cognitive function) and secondary outcomes (functionality, emotional state, and fragility) will be examined through a two-way analysis of covariance (ANCOVA), with the intervention group (control or experimental) included as a fixed factor. The differences between initial results and those after intervention, as both the dependent variable and covariates, will include intervening study variables such as age, gender, education level, marital status and occupation. The difference in means will be calculated using Cohen’s d to evaluate effect size. Group differences in intervening variables will be analyzed using independent samples t-tests for continuous variables (e.g., age). The chi-square test will be used to investigate group differences in categorical variables (e.g. gender). Significant values will be considered for p-values less than 0.05, with a 95% confidence interval. IBM SPSS Statistics software version 28.0.1 will be used for statistical analysis”.

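### The trial is sized on everyday cognition (PECC) alone, yet PECC and MoCA are both declared primary at an unadjusted 0.05 with no rule for how the two results combine.

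*Protocol article*

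**What the plan says.** Three sections of the protocol article bear on this.

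- **Sample size.** Everyday cognition is the primary variable: "The primary variable chosen in both studies was everyday cognition". The calculation uses only that variable. The experimental arm of the source trial "demonstrated an improvement of 2.57 points in the primary variable", against 0.39 points in its control arm. The error level is set by "A one-sided approach has been assumed with a confidence level of 95% and a statistical power of 80" percent.
- **Description of the variables.** The sentence opens in the singular but lists two measures: "The primary variable will be everyday cognition, measured by the Test for the Evaluation of Everyday Cognition (PECC) and cognitive performance", the second of them "measured by the Montreal Cognitive Assessment Test (MoCA").
- **Data analysis.** The wording is now plural: "The effects of the intervention on primary outcomes (everyday cognition and cognitive function) and secondary outcomes (functionality, emotional state, and fragility"). Both are to be analysed by ANCOVA, and the decision threshold is "Significant values will be considered for p-values less than 0.05, with a 95% confidence interval".

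No section says whether one significant primary outcome is enough, whether both are needed, or whether one is tested before the other. The Aim section gives a single hypothesis spanning cognitive function, emotional state, frailty and functionality, and no success criterion. No expected effect or power is given for MoCA.

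**The concern.** The document gives two answers to how many primary outcomes there are. Sample size points to one; the other two sections point to two. With two tests each read at 0.05 and no combination rule, a report could present either outcome as the trial's primary success. The 5% level would then not describe the chance of a false primary claim.

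If instead both outcomes had to be significant, the error would be controlled, but the 80% power stated for one outcome would not be the power of the trial. And if one outcome is significant and the other is not, the plan does not say whether the hypothesis has been supported.

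**Working it through.** **Inputs from the protocol article**
- Primary outcomes: PECC and MoCA (Description of the variables; Data analysis).
- Threshold per test: 0.05, with no adjustment and no sidedness stated (Data analysis).
- Sizing: one-sided 5%, 80% power, equal arms, improvements of 2.57 and 0.39 points, 20% loss, N = 99 (Sample size).

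**Assumed:** the correlation between the two test statistics. The document gives none, so a range is shown.

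**1. The plan's own N.** The difference is 2.57 − 0.39 = 2.18. After 20% loss, 99 × 0.8 = 79.2 remain, or 39.6 per arm. The article does not print the SD, so N cannot be reproduced directly. Solving n = 2(z₀.₉₅ + z₀.₈₀)² SD² / 2.18² for the SD at n = 39.6 gives SD ≈ 3.90. So 99 is consistent with a one-sided 5% test on PECC alone if the SD was about 3.90. Nothing in the error rates below depends on this SD.

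**2. Either outcome counts as success.** For independent tests the family-wise error is 1 − (1 − 0.05)² = 1 − 0.9025 = 0.0975. The Bonferroni bound, whatever the correlation, is 0.05 + 0.05 = 0.10. For correlation r, one minus the bivariate-normal probability that neither test rejects gives:

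| r (assumed) | two-sided 0.05 | one-sided 0.05 | two-sided 0.05, errors favouring the experimental arm only |
|---|---|---|---|
| 0 | 9.75% | 9.75% | 4.9% |
| 0.3 | 9.5% | 9.3% | 4.8% |
| 0.5 | 9.1% | 8.8% | 4.5% |
| 0.7 | 8.3% | 8.0% | 4.2% |

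The nominal level is 5% in the first two result columns and 2.5% in the last.

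**3. Both outcomes required.** The chance that both tests reject falsely cannot exceed that of either one, so the error is at most 5%. Power cannot exceed the smaller of the two single-outcome powers. As an illustration, suppose MoCA also had 80% power, which the document does not claim. With independent tests, joint power is 0.80 × 0.80 = 64%.

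**4. Alpha split, 0.025 each.** The family-wise error for independent tests is 1 − 0.975² = 4.94%, and at most 5% in any case. At the back-solved SD of 3.90 (an assumption), a one-sided 0.025 test of PECC needs 2(1.960 + 0.842)² × 3.90² / 2.18² ≈ 50.2, so 51 per arm. That is 102 / 0.8 = 127.5, so 128 in total. At 39.6 per arm, PECC power falls from 80% to about 70%.

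**5. PECC first, MoCA only if PECC is significant.** A false claim on PECC has probability at most 5%. MoCA can be claimed only after PECC has passed, so the pair is held at 5%. PECC keeps its full level and the stated sizing basis.

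**6. Secondary outcomes.** Description of the variables lists FIM (functionality), Yesavage (emotional state), the Frailty Index, and Lawton and Brody (instrumental activities). The parenthesis in Data analysis has functionality, emotional state and fragility. Because functionality is defined as FIM, with instrumental activities listed separately, the Lawton and Brody scale is not covered by that word.

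**The case against.** The strongest objection is that a multiplicity procedure is commonly left to the statistical analysis plan, which is not shown. That disposes of any complaint that a procedure is merely missing. It does not dispose of this point: the article itself declares two primary outcomes, fixes the 0.05 threshold and sizes the trial on one of them.

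It can also be said that sizing on one of two primary outcomes does not deny that the other is primary, and that the Sample size sentence was written to justify the choice of source study. That softens the conflict. It still leaves MoCA without a stated power and the decision rule open.

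Three stronger readings may tempt a reader, and the document supports none of them.

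- **That the false-claim rate is nearly 10% as a fact.** This needs both independence and an either-outcome rule. The document neither states nor excludes that rule. Two cognitive scores from the same people are probably positively correlated, which lowers the figure. If the tests are two-sided and only errors favouring the experimental arm count, the rate is 4.2% to 4.9% against a nominal 2.5%.
- **That PECC and MoCA should be expected to move in opposite directions.** The control programme does train functions that MoCA scores. But the Interventions section says the experimental tasks also draw on attention, reasoning, working memory and planning. A reversal is conjecture.
- **That clustering of participants within centres compounds the figure.** That is a separate matter and does not enter this calculation, which takes each test's nominal level as valid.

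**Conclusion.** The point holds in a conditional form. The article conflicts with itself on whether there is one primary outcome or two, and it attaches an unadjusted 0.05 to both without saying how they combine. Under an either-outcome reading, the family-wise error is 9.75% with independent two-sided tests, and 9.1% or 8.3% at assumed correlations of 0.5 or 0.7. Under a both-required reading there is no inflation, but the 80% power no longer describes the trial's primary conclusion. These figures rest on the assumed correlations and on each single test holding its nominal level; they do not depend on the unprinted SD.

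The missing Lawton and Brody scale is a minor, separate inconsistency with no bearing on the primary error rate.

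**What to change.** In Description of the variables and in Data analysis, name PECC as the single primary outcome, as the Sample size section already assumes. Make MoCA the first secondary outcome, tested at 0.05 only if PECC is significant (fixed sequence). This is a wording change. PECC keeps its full alpha and no extra participants are needed. The cost is that MoCA alone can no longer carry a primary claim.

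If the investigators wish to keep both as primary, they should state one of these rules before any unblinded analysis and restate power:
- **Both required:** no alpha adjustment, but joint power is lower and an expected effect for MoCA must be given.
- **Alpha split (for example 0.025 each):** PECC power drops to about 70% at the planned size, or the total rises to about 128, both at the back-solved SD of 3.90.

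In either case, state in Data analysis whether the tests are one-sided or two-sided, so that it agrees with the one-sided Sample size section. Separately, reconcile the two secondary lists, either by adding the Lawton and Brody scale to the analysed outcomes or by saying why it is not analysed.

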### Sample/Participants

#### Participants

The study population will be composed of people aged 60 years or older without cognitive impairment who voluntarily agree to participate in the Occupational Therapy programme of the Geriatric Revitalisation project organised by the University of Salamanca in collaboration with the Salamanca City Council (Spain), within the framework of the Research in Active Ageing agreement. Regarding the location, the study will be carried out in eleven municipal centres and associations for the elderly belonging to the Salamanca City Council, Spain. The researchers of the University of Salamanca will invite older adults to participate in the study by explaining the details of the clinical trial and they can be included once they have given their verbal and written consent and meet the following selection guidelines: (A) Inclusion criteria: Being 60 years of age or older, voluntarily signing the informed consent form authorising participation and completing the initial assessment. (B) Exclusion criteria: Not having knowledge of reading and writing or significant deficits in language comprehension, being institutionalised, to have a clinical diagnosis of a neurocognitive disorder included in the DSM-V at the time of the initial assessment and participating in another cognitive stimulation programme. (C) Withdrawal criteria: Dropping out of the programme.

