### Tools employed in the evaluation of the variables

Test For The Evaluation Of Everyday Cognition (PECC)" [17]: measures the ability of older people to solve 12 real situations grouped into the following areas: medication, administrative management, financial management, meal preparation, transport and shopping, thus allowing to know the functional capacity of their daily life. The administration time is 35 minutes.The Montreal Cognitive Assessment Test (MoCA test) Version 8.3 [18]: allows the detection of mild cognitive impairment (MCI) by assessing executive functions, attention, abstraction, memory, language, visual-constructive abilities, calculation and orientation. The administration time is 10 minutes. The maximum score is 30 points, below 26 points being the cut-off for MCI (in developed countries).Yesavage Geriatric Depression Scale [19]: questionnaire for depression screening in people over 65 years of age. Administration time is 5 minutes. A score above 5 shows moderate depression and above 10 shows severe depression.Functional Independence Measure (FIM)" [20]: measures the level of functionality and assistance given by the caregiver. It assesses activities of daily living subdivided into motor and cognitive dimensions. Each of the 18 items has a maximum score of 7 and a minimum score of 1, making a total of 126 items."FRAIL frailty scale" [21]: provides a quantitative measure of frailty in geriatric patients. The maximum score is 5 points."Lawton and Brody Scale" [22]: designed to assess autonomy in instrumental activities in the elderly population. It takes 4 minutes to administer and is scored 0 or 1 for each of the items, with a total score of 8."ARMS-e Questionnaire" [23]: analyses in a multidimensional way the lack of adherence in multi-pathological patients, allowing individualised assessment of the barriers detected in adherence problems."Medical Outcomes Study (MOS) Questionnaire" [24]: allows us to quickly and simply assess social support in a global manner, but also allows us to ascertain the emotional, instrumental, affective and positive social interaction dimensions.

An individual data collection sheet will be used for each participant and recorded in a database designed specifically for this study.

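### FIM and FRAIL may leave this sample little room to improve, and comparing mean change without the baseline score loses further power

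*Protocol article*

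**What the plan says.** **Secondary outcomes** (Description of the variables). The list reads: "Secondary variables will be functionality (Functional Independence Measure, FIM), emotional state (Yesavage Scale), frailty (Frailty Index) and independence in instrumental activities of daily living".

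**Population** (Participants section). The study enrols "people aged 60 years or older without cognitive impairment who voluntarily agree to participate in the Occupational Therapy programme". Exclusions include "being institutionalised, to have a clinical diagnosis of a neurocognitive disorder included in the DSM-V at the time of the initial assessment". No criterion concerns baseline function, frailty or independence in instrumental activities.

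**Instruments** (section on the tools employed). FIM "measures the level of functionality and assistance given by the caregiver", and its range is described as "Each of the 18 items has a maximum score of 7 and a minimum score of 1, making a total of 126 items", so the best total is 18 × 7 = 126 points. Lawton-Brody "is scored 0 or 1 for each of the items, with a total score of 8". The frailty measure is called a Frailty Index in the description of the variables, but the instrument described is the FRAIL scale with a maximum of 5. Its minimum and direction are not stated; I take 0 as the best score.

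**Aim.** The Abstract and the Aim look for greater benefit on functionality and frailty, among other domains. The Background also speaks of maintaining function.

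**Analysis** (Data analysis section). The primary outcomes, and functionality, emotional state and fragility as secondary outcomes, "will be examined through a two-way analysis of covariance (ANCOVA") on the difference between initial and final results, with Cohen's d. The covariates given as examples are age, gender, education, marital status and occupation. The histogram check for normality decides only between mean with SD and median with interquartile range as descriptive statistics. It does not alter the group comparison.

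**The concern.** A person already at 126 on FIM, or at the best frailty score, can stay the same or worsen but cannot improve. The entry rules select people who live outside institutions and attend a weekly class, so a sizeable share could start at or near those limits. Mean change then averages over people who have no room to gain, and the arm difference shrinks even if the training works.

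Functionality and frailty are two of the four domains in the stated hypothesis, and transfer to daily functioning is the argument for the new programme. A null result on these scales could be taken as evidence against transfer when it says little either way. The Limitations section does not mention ceiling or floor effects. Separately, a change score not adjusted for its own baseline discards information that the trial already collects.

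**Working it through.** **The plan's own figure.** The protocol gives no power or expected value for FIM, FRAIL or Lawton-Brody. Its only figure is 99 participants, sized on everyday cognition (difference 2.57 − 0.39 = 2.18, one-sided 5%, 80% power, 20% loss). No SD is stated, so 99 cannot be reproduced, only back-solved. With 40 evaluable per arm, the standardised effect is (1.645 + 0.842)/√(40/2) = 0.556, implying an SD of 2.18/0.556 = 3.92.

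**Inputs for the illustration.**
- From the protocol: 99 × 0.8 ≈ 79 completers, taken as 40 per arm.
- Assumed: normal latent score, pre-post correlation 0.8, true arm effect 0.5 latent SD, two-sided 5%, independent participants.
- Varied: the share at the best score at baseline, since the documents do not give it.

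**Without a limit.** The SD of change is √(2 × (1 − 0.8)) = 0.632, so d = 0.5/0.632 = 0.79. Power is Φ(0.79 × √20 − 1.96) = Φ(1.57) ≈ 94%.

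**With a limit.** Both scores are capped at the value that leaves the stated share at the limit at baseline. The number able to improve is 79 × (1 − share). The third column is the simulated difference in mean change (0.332, 0.155, 0.090, 0.032) divided by 0.5. Power is simulated with the score recorded in steps of 0.5 latent SD, like a coarse scale.

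| Share at best score | Able to improve, of 79 | Mean difference kept | Power, change score | Power, final score adjusted for baseline |
|---|---|---|---|---|
| 25% | 59 | 66% | 81% | 88% |
| 60% | 32 | 31% | 52% | 68% |
| 75% | 20 | 18% | 35% | 49% |
| 90% | 8 | 6% | 15% | 20% |

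Without the steps, power at 60%, 75% and 90% is 47%, 30% and 14% for the change score, and 62%, 43% and 20% with baseline adjustment. The pattern is the same. Adjustment reduces the residual SD but leaves the mean difference as attenuated as before.

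**Second set of assumptions.** With correlation 0.7 and the back-solved effect of 0.556 SD of change, the share of the true effect kept is 67%, 41%, 23% and 7% at 25%, 50%, 70% and 90% at the limit. Two-sided power for the change score falls from 70% without a limit to 54%, 38%, 24% and 11%. One-sided, it falls from 80% to 66%, 50%, 35% and 17%.

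**Ordinal model.** In a check of 500 runs at 60%, 75% and 90% at the limit, a proportional-odds model with a Wald test had power of 71%, 50% and 5%. The linear model adjusted for baseline had 68%, 53% and 17%. The ordinal model adds little at 60% to 75%, and its Wald test fails at 90%.

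**The case against.** The strongest reply is that the premise is not in the documents. No baseline distribution is given. The exclusions do not remove people with physical disability, frailty or dependence in instrumental activities, and recruitment is from an occupational therapy programme. That stands: the share at the limit is an inference, and at 25% the loss is modest.

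A reader might infer that mean change on these scales cannot register any benefit. The documents do not support that. The signal is attenuated but not zero, and an arm difference can also arise through less worsening, which fits the Background's wording on maintaining function.

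A reader might also infer that all three scales go into this ANCOVA. The Data analysis section names functionality, which the description of the variables ties to FIM, and fragility. It does not name Lawton-Brody or instrumental activities, so the point reaches that scale only if it is analysed the same way.

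Nor do the documents show that a null result will be misread. These are secondary outcomes, and everyday functioning is also measured by a primary one, the PECC. That a null result could be misread is as far as one can go.

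Finally, an unseen analysis plan may hold the tables and the treatment of non-normal outcomes. That is fair for the tables. But the article itself fixes the change score as dependent variable. Its covariate list is introduced by examples, so baseline could be added later. If it is, the arm effect from the change score equals that from the final score, and this part of the point is met.

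**Conclusion.** The point holds as a conditional weakness in secondary outcomes. Bounded dependency and frailty scales are used with improvement as the aim in a sample not selected for any limitation. The stated comparison is mean change with no baseline score named as covariate.

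If a quarter start at the best score, about two thirds of a true mean improvement is kept. If nine in ten do, 6% to 7% is kept. Under the first set of assumptions, baseline adjustment recovers between 5 and 16 percentage points of power, depending on the share at the limit.

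These figures rest on an assumed latent normal score, correlation and effect. They ignore that eleven groups, not individuals, are randomised, so the absolute powers do not describe this trial. The direction of the comparison and the shrinkage with the share at the limit are what should be relied on.

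**What to change.** For FIM and FRAIL, and for Lawton-Brody if it is analysed the same way:

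- Replace the change score with the final score adjusted for its own baseline value, handling the randomised groups as in the main model.
- Use a proportional-odds model with a likelihood-ratio test only as a sensitivity analysis.
- Tabulate by arm the number at the best score at baseline, and the numbers worsened, unchanged and improved.
- Word the objective for these scales as maintenance or improvement, in line with the Background.
- State in advance that no difference on a scale where most started at the best score is uninformative and will not be reported as no effect on functionality.

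Retaining or dropping Cohen's d is a matter of preference.

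The cost is a little more analysis and some rewording. Instruments and visits are unchanged. These outcomes will remain imprecise, because adjustment does not create headroom.
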